| --- | --- |

1. **Study design**

| **3.1**  **a. General description of the study design** | This research project will use the data infrastructure Extramural Leiden Academic Network (ELAN).  ELAN provides access to and the use of pseudonymized healthcare data from various cooperating partners such as healthcare data of general practitioners. The study period concedes 2014-2024.  ***Question***  Is antibiotic use associated with increased risk for urinary tract infection in adults?  Further explorations will be done to what extent the increased UTI risk of antibiotic use holds for:   - Different antibiotics or antibiotic classes - Men versus women - Post- versus Premenopausal women - Indication for antibiotic treatment (excluding UTI’s)   A self-controlled cases series (SCCS) design will be employed to establish the risk for developing an UTI within 3 months after antibiotic treatment compared to patients with an UTI who did not receive an antibiotic treatment. With the SCCS design, patients will be their own control.  The primary endpoint is risk of a UTI within 3 months after initiation of antibiotic treatment computed as an odds ratio.  An antibiotic treatment is defined as the exposure. An UTI between 2 weeks and 3 months after antibiotic treatment is defined as an event. The first 2 weeks after start of the treatment, patients are still somewhat protected by the antibiotic use against a new infection. And if a new antibiotic treatment is needed within 2 weeks after start of treatment, this is considered as treatment failure of the initial treatment.  Descriptive analysis will be performed for exposures, outcomes and covariables for the whole population of analysis and stratified by antibiotic use or not.  Multivariable logistic regression analysis will be performed to assess whether there is an association of antibiotic use with developing a UTI within 3 months after initiation of treatment. First a crude model will be used followed by confounder adjusted models. Confounders are season variability (Winter, spring, summer and autumn) and risk factors for UTI and selected based on theory or literature (Tj VanderWeele 2019). Risk factors are a history of an UTI, urine incontinence, urolithiasis, pregnancy, urine catheter, anatomical / functional abnormality urinary tract, immunocompromising comorbidities such as HIV/AIDS ,Type 2 Diabetes Mellitus.  **Subgroup analysis**  Subsequently, subgroup analysis will be performed to examine whether the association differs upon specific type of antibiotic treatment. For each subgroup, we will calculate an odds ratio for an UTI after antibiotic treatment. Subgroups are antibiotic(group)s, gender and age, type of infection and social determinants .  *Most used antibiotic(group)s in primary care*:   - Amoxicillin - Amoxicillin/clavulanic acid - Flucloxacillin - Tetracyclines - Macrolides - Fluoroquinolones - Trimethoprim - Co-trimoxazole - Fosfomycin - Nitrofurantoin   *Type of infection*   - All infections - UTI - non-UTI (all other infections)   *Gender and age*   - Men - Premenopausal women, defined as < 50 years of age - Postmenopausal women, defined as ≥ 50 years of age   *Social determinants*   - Socio-economic status (SES) - Migrant background |

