| --- | --- |
| **3.2**  **a. When will the study be conducted?**  **b. What is the intended end date of the study?** | The research will be performed as part of a MSc. Internship ([name]) in the period between February 2025 and June 2025.  Month 1 – Literature research, writing the introduction, first part of data preparation.  Month 2 – Writing the introduction and methodology, second part of data preparation.  Month 3 – Completing the introduction, methodology and data preparation, start of data analysis.  Month 4 – Completing the data analysis and writing the results.  Month 5 – Writing the report, focusing on the discussion.  The end date is July 2025. |
| **3.3**  **Does the study involve exclusively existing (patient) data (retrospective) and not data yet to be generated (prospective)?** | This study includes already existing data only, and is thus retrospective (see also 3.1). |
| **3.4**  **What type of data will be used for the research?** | Pseudonymized routine care patient data from GP practices participating in ELAN. |
| **3.5**  **If information from patient records is used: describe what type of information is involved.** | The dataset from ELAN contains data over a period of 10 years and includes:   - Number of all included patients in ELAN per year - All patients with an UTI   - ICPC code U70, U71, including subcodes   - Date of registration with GP office - Antibiotic prescriptions ATC J01 for all patients with an UTI   - Corresponding medical diagnosis with the antibiotic prescription by ICPC code   - Details on the antibiotic prescription (name of antibiotic, dose and duration) - Characteristics of included patients   - Year of birth   - Year of death   - Sex   - Referral to urologist for recurrent UTIs   - Risk factors for an UTI     - History of UTI ICPC code U70, U71     - Urine incontinence ICPC code U04     - Urolithiasis ICPC code U95     - Urine catheter ICPC code U28     - Anatomical / functional abnormality urinary tract ICPC code U85     - Type 2 Diabetes Mellitus ICPC code T90.02     - Prostate hypertrophy ICPC codes Y06, Y85     - Medication use for miction problems with ATC codes     - G04BD     - G04C     - Social economic status     - Migrant background |
| **3.6**  **To which time period do the data relate?** | The period between 2014 and 2024 |

1. **Data storage and privacy**

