| **4.10**  **If coding takes place: when will coding occur, by whom, and in what manner?** | Coding is done by STIZON and CBS |
| **4.11**  **Has a notification of the intended data processing been submitted via:**  <https://www.albinusnet.nl/weten-en-regelen/juridische-zaken/privacy/meldenverzamelenonderzoeksdata/>**?** | Yes |
| **4.12**  **If applicable: where will the coded data be stored, and who will have access to the coded data?**  **If applicable: where will the uncoded data be stored, and who will have access to the uncoded data?** | The coded data is stored, and a specific research folder assigned to the department disk (I: \) of PHEG. Only the researchers involved ([name] and [name]) and the PHEG data manager have access to this folder.  There is no storage of uncoded data. |
| **4.13**  **What technical and organizational measures have been taken to prevent loss, theft, or unauthorized use of the research data? For example, is a data safe being used?** | The data never physically leaves the research folder of the LUMC or the remote access CBS environment and see 4.12. |
| **4.14**  **By whom is the code key managed?** | STIZON. |
| **4.15**  **Will (research) data be shared with another institution(s) within the Netherlands and/or the EU?** | No. |
| **4.16**  **a. Will (research) data be shared with another institution/organization outside the EU?**  **b. Will the relevant patients be asked for consent to share their personal data with a country outside the EU?** | No.  Not applicable. |
| **4.17**  **How long will the (research) data be retained? If the data will be kept for longer or shorter than the standard retention period of 15 years, please explain why.** | After processing, the research data is returned to ELAN in accordance with the data transfer agreement. The LUMC department PHEG will keep the research data for 15 years. |

1. **Research population**

| **5.1**  **Inclusion criteria** | Adults patients 18 year and older with an acute UTI and registered at an GP office for a least 1 year |
| --- | --- |
| **5.2**  **Exclusion criteria** | Patients younger than 18 years of age.  Patients with antibiotic prophylaxes  UTIs are excluded as an event if   - During pregnancy - within 3 months after giving birth - within 1 year prior to an UTI (wash-our period) |

1. **Statistical analysis**

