| **6.1**  **a. Primary outcome**  **b. Secondary outcome** | ***Primary outcome***  What is the association of antibiotic use for any infection with risk for urinary tract infection in adults?   - Odds ratio for an UTI after antibiotic use in the preceding 3 months   - Per infection group, antibiotic for     - All infections     - An UTI     - An infection expect UTI’s   - Per antibiotic (group)   - Per patient group     - Men     - Women < 50 years of age     - Women ≥ 50 years of age   - Social determinants     - SES     - Migrant background   - Combinations of each subgroup   ***Secondary outcome***   - Hazard ratio for an UTI after antibiotic use in the preceding 3 months   - Per infection group, antibiotic for     - All infections     - UTI     - non-UTI   - Per antibiotic group   - Per patient group     - Men     - Women < 50 years of age     - Women ≥ 50 years of age   - Social determinants     - SES     - Migrant background   - Combination of each subgroup - Incidence of an UTI per month |
| --- | --- |
| **6.2**  **a. Statistical analysis primary outcome**    **b. Statistical analysis secondary outcome** | ***Primary outcome***  The Odds ratio for an UTI after antibiotic treatment the preceding 3 months will be calculated through a logistic regression model.  Risk factors and season variability are defined as confounders in this logistic regression model. Risk factors are a history of an UTI, urine incontinence, urolithiasis, pregnancy, urine catheter, anatomical / functional abnormality urinary tract and Type 2 Diabetes Mellitus. An Odds ratio for an UTI will be attributed to each confounder based on a critical literature appraisal.  ***Secondary outcome***  Cox proportional hazard regression models will be used to examine the associations between an UTI after antibiotic treatment the preceding 3 months.  Survival time (in days) was defined as the period between 14 days after the start of the antibiotic treatment and an UTI. The hazard ratio will be adjusted with the previous described confounders (see primary outcome).  The incidence of each UTI will be calculated for each month during 10 years to examine the season variability. |

1. **Appendices and references**

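### The Cox survival time in Section 6.2 exists only for antibiotic courses, drops the 3-month limit of Section 3.1, and would be fitted to UTI cases under Sections 5.1 and 3.5

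*Protocol*

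**What the plan says.** - **Quantity wanted.** Section 6.1 lists as a secondary outcome: "Hazard ratio for an UTI after antibiotic use in the preceding 3 months". It is planned by infection group, antibiotic group, patient group, social determinant and combinations of these.
- **Model.** Section 6.2: "Cox proportional hazard regression models will be used to examine the associations between an UTI after antibiotic treatment the preceding 3 months".
- **Time scale.** Section 6.2: "Survival time (in days) was defined as the period between 14 days after the start of the antibiotic treatment and an UTI".
- **Event.** Section 3.1: "An UTI between 2 weeks and 3 months after antibiotic treatment is defined as an event".
- **Comparator.** Section 3.1 gives two. One is between patients: "compared to patients with an UTI who did not receive an antibiotic treatment". The other is within patients: "With the SCCS design, patients will be their own control".
- **Population.** Section 5.1 admits "Adults patients 18 year and older with an acute UTI and registered at an GP office for a least 1 year". Section 3.5 requests "Antibiotic prescriptions ATC J01 for all patients with an UTI". Section 4.5 instead says that the data of all adults in the warehouse are used.

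**The concern.** A hazard ratio for antibiotic against no antibiotic needs a clock for both sides. The clock in Section 6.2 starts at a date that only an antibiotic course has. A patient or a period without antibiotics gets no survival time, so the analyst must invent an origin that the protocol does not supply.

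Two further features make that choice matter. First, the clock stops only at a UTI. The definition names no end at 3 months, at death, on leaving the practice or at the end of the data. Second, under Sections 5.1 and 3.5 the model would be fitted to people selected for having the outcome, and an ordinary Cox model makes no allowance for that.

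At stake is the whole set of secondary hazard ratios. A reader would take them as support for the primary odds ratios, yet their value could reflect the chosen origin and length of follow-up more than any effect of antibiotics.

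**Working it through.** The protocol gives no hazard ratio, event count or sample size to reproduce, so the check has three parts.

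**1. Which records have a survival time?**

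| Time to be compared | Start under Section 6.2 | End under Section 6.2 |
|---|---|---|
| Antibiotic course | Day 14 after start | A UTI, no other end stated |
| UTI patient without antibiotics (3.1) | None | Cannot be computed |
| Patient's own unexposed time (3.1) | None | Cannot be computed |

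Neither comparator of Section 3.1 fits the time scale of Section 6.2.

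**2. How many UTIs would fall after 3 months if Section 6.2 is applied literally?**

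Inputs from the protocol:
- Section 2.1 gives 20 UTIs per 1,000 men and 117 per 1,000 women per year, so λ = 0.020 and 0.117.
- Section 2.1 also gives recurrence of 20–30% in 3–4 months. At a constant hazard this is λ = −ln(0.8)/(4/12) = 0.669 to λ = −ln(0.7)/0.25 = 1.427 per year.
- The window of Section 3.1 is w = 0.25 − 14/365.25 = 0.2117 year, about 77 days.

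Assumptions: constant hazards, a rate ratio R of 1, 2 or 3 inside the window, and follow-up of T years from day 14.

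- Inside the window: A = 1 − exp(−λRw)
- After the window: B = exp(−λRw) × [1 − exp(−λ(T − w))]
- Share after 3 months: B/(A + B)

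Example for women, R = 1, T = 10: A = 1 − exp(−0.117 × 0.2117) = 0.0245 and A + B = 1 − exp(−1.17) = 0.690. The share after 3 months is 1 − 0.0245/0.690 = 96.5%.

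| UTI rate per year | T = 0.5, R = 1 to 3 | T = 1, R = 1 to 3 | T = 10, R = 1 to 3 |
|---|---|---|---|
| 0.020 (men) | 58% to 31% | 79% to 55% | 98% to 93% |
| 0.117 (women) | 57% to 30% | 78% to 53% | 97% to 90% |
| 0.669 (20% in 4 months) | 54% to 25% | 73% to 44% | 87% to 65% |
| 1.427 (30% in 3 months) | 49% to 19% | 66% to 31% | 74% to 40% |

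If the event definition of Section 3.1 is enforced, the share is 0% in every row.

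**3. What do the open choices do to the hazard ratio?**

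Simulation: 60,000 persons, 10 years, rate 0.117 per year, and one course at a random date in half of them. Time runs to the first UTI. Exposed records are courses still UTI-free at day 14; unexposed persons never have a course. Two origins were tried for the unexposed.

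| Population | Stop | Origin of unexposed | True ratio 1 | True ratio 2 | True ratio 3 |
|---|---|---|---|---|---|
| UTI cases only | None | Start of data | 1.58 | 1.65 | 1.74 |
| UTI cases only | None | Random index date | 0.99 | 1.05 | 1.08 |
| UTI cases only | 3 months | Start of data | 1.31 | 2.73 | 4.17 |
| UTI cases only | 3 months | Random index date | 0.93 | 1.76 | 2.90 |
| All patients | None | Either | 1.00 | 1.05 | 1.08 |
| All patients | 3 months | Start of data | 0.90 | 1.90 | 2.90 |
| All patients | 3 months | Random index date | 0.87 | 1.95 | 2.71 |

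The values with a 3-month stop carry simulation error of roughly 10%. Three things follow:
- Without a stop, a true doubling confined to the window shows as 1.05, even with all patients.
- In cases only, the origin alone moves a null result from 0.99 to 1.58.
- Adding the 3-month stop does not cure a poor origin: the null value is still 1.31.

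**The case against.** The best defence is that the survival-time sentence should not be read alone. Section 3.1 limits the event to 2 weeks to 3 months, and both the outcome label in Section 6.1 and the Cox sentence in Section 6.2 repeat the 3-month period. Section 3.1 also names an untreated comparator. Index dates and censoring rules are commonly left to a SAP, which is not shown, and this is a secondary analysis.

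Much of this stands, and it rules out three stronger readings:
- **That the hazard ratio mostly counts UTIs outside the window.** This needs Section 6.2 to be applied literally with long follow-up. It is not reliable with 6 to 12 months of follow-up or at the recurrence rates, and it is false if Section 3.1 is enforced. The documents show a limit that was not carried over, not a plan without one.
- **That nearly every record ends in an event.** Section 5.1 requires a UTI, not a UTI after the course in question. The qualifying UTI may precede the course or be the infection it treated, since antibiotics for UTI are a planned exposure group. The simulated cases all have their UTI after the course, so those rows show the selection at its strongest.
- **That the case-only population is settled.** Sections 5.1 and 3.5 say so, but Section 4.5 says all adults. Selection on UTI is also not harmful under every choice: with a random index date and a 3-month stop, the case-only results lie near the truth.

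The defence does not supply a time zero for unexposed time. The protocol fixes a survival time that neither comparator can have, so a SAP would have to replace that definition rather than add to it.

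**Conclusion.** Wrong as written, in a secondary analysis. Followed as stated, Section 6.2 yields no valid antibiotic-versus-none hazard ratio for UTI within 3 months. Unexposed time has no origin, the 3-month limit is not in the time definition, and Sections 5.1 and 3.5 conflict with Section 4.5 on who is analysed.

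No single figure gives the size of the error, because it depends on choices the protocol leaves open. The range runs from no UTI counted outside the window, if Section 3.1 is enforced, to 98% for men over 10 years with no antibiotic effect. A null effect can appear as 0.99 or 1.58 according to the origin alone. These figures rest on constant hazards, assumed rate ratios of 1 to 3 and, in the simulation, one course in half of the patients and no confounding. They show that the result is sensitive, not what this study would find. The point does not bear on the primary odds ratio.

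**What to change.** **Preferred.** Replace the Cox analysis in Sections 6.1 and 6.2 by self-controlled case series rate ratios for 2 weeks to 3 months after an antibiotic start, against each patient's own unexposed time. The window can be split into sub-intervals (for example days 14–30, 31–60 and 61–90) if timing is of interest. This fits the design declared in Section 3.1 and uses the planned extract of UTI patients, so the cost is wording and code. One caution: a UTI itself leads to a prescription, so later exposure depends on the event. That applies to the design already chosen in Section 3.1, and the analysis must deal with it.

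**If a hazard ratio is kept.** Treat antibiotic exposure as time-varying, with a person exposed only from 2 weeks to 3 months after a start. Give exposed and unexposed time a common origin and the same stated censoring, and reconcile Section 4.5 with Sections 3.5 and 5.1. This is more than rewording. Section 3.5 requests prescriptions only for UTI patients and Section 4.5 does not mention antibiotics, so the extract must be widened to adults without a UTI. Section 3.5 also lists the registration date and year of death but no date of leaving the practice, so the end of follow-up needs checking.

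Under either option, state one comparator in Section 3.1 and use it throughout.
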